## Abstract

**Background:**

Pre-exposure prophylaxis (PrEP) is an effective approach for preventing HIV infection, but it is underutilized by populations who may benefit the most, including people living in the Southern United States and those involved in the criminal legal (CL) system. Improving the access and use of PrEP for these groups could decrease HIV-related health disparities. Beyond individual outcomes, HIV prevention for CL-involved people can have a significant public health impact on HIV incidence due to a high turnover between jails and the community.

**Objective:**

We will develop, implement, and evaluate a multicomponent PrEP implementation strategy for the Dallas County Jail (DCJ) to increase the initiation of this HIV-preventive intervention for CL-involved individuals.

**Methods:**

This is a type 3 hybrid implementation-effectiveness study that takes a combined approach by assessing the implementation of a strategy to identify candidates for PrEP at the DCJ and linking them to PrEP providers upon community re-entry while also gathering information about clinical outcomes. The approach is guided by the EPIS (exploration, preparation, implementation, sustainment) framework. Initial formative work (exploration) involves qualitative interviews of diverse key stakeholders to identify factors that may influence linkage to PrEP after jail release. These findings will undergo rapid qualitative analysis (preparation) to inform the adaptation of a multicomponent jail PrEP implementation strategy protocol. This approach, which will include an electronic health record (EHR) prediction model and integration of a PrEP patient navigator into the jail health team, will allow medical providers and the navigator at the DCJ to engage individuals most likely to benefit in shared decision-making about PrEP and navigate them to community PrEP care (implementation) in a process that begins before release from jail and ends with successful care linkage. Regular quantitative and qualitative evaluations of this approach will allow for ongoing stakeholder input, refinement of the implementation strategy, and maintenance of the program (sustainment).

**Results:**

Findings from 26 qualitative interviews (9 formerly incarcerated individuals, 9 county jail staff, and 8 employees of community organizations) have been obtained, analyzed, and mapped to an implementation strategy formalized in a jail PrEP protocol. An HIV risk prediction model based on EHR data to identify individuals most likely to benefit from PrEP has been developed and internally validated and is ready to be deployed. We anticipate the availability of preliminary study findings in 2026.

**Conclusions:**

This study will provide key insights into the feasibility and effectiveness of a PrEP implementation strategy among people at increased risk of HIV acquisition in an urban jail in Southern United States. This practical and scalable strategy can be used as a model for other urban jails to address HIV-related inequities.

**International Registered Report Identifier (IRRID):**

DERR1-10.2196/64813

## Introduction

It was estimated that there were 31,200 new HIV infections across the United States in 2021 [1], with a disproportionately high percentage of new diagnoses occurring in the South [2]. New HIV infections disproportionately affect men who have sex with men (MSM) and Black and Hispanic populations [3]. HIV prevention with pre-exposure prophylaxis (PrEP) can reduce the risk of HIV acquisition by 99% [4,5], but its public health impact depends on connecting populations at risk of HIV to PrEP care and continuing care over time [6-9]. Uptake of PrEP is increasing among White MSM on the east and west coasts but remains limited in minority groups in the South [10-12] where HIV incidence is the highest [13]. The PrEP-to-need ratio, defined as the number of PrEP users divided by new HIV diagnoses [14], is lower in the South than in any other region, particularly among racial and ethnic minorities, further highlighting inequitable access [15].

To decrease HIV incidence, there is a need to improve PrEP use in populations most heavily impacted by HIV. Launched in 2019, the federal *Ending the HIV Epidemic* (EHE) initiative provides an evidence-based framework for decreasing HIV incidence in the United States by 90% by 2030 [16]. The EHE initiative identifies that a critical component of epidemic control is to focus prevention efforts on geographic hotspots, including the 48 counties with the highest incidence, which are disproportionately in the Southern United States, and 7 states with major rural HIV epidemics. Active multisector partnerships among local public health departments, health care facilities, academic institutions, and community organizations are pivotal to achieving the EHE initiative’s goal [8,17].

Dallas County in Texas is one of the largest HIV hotspots in the South, with high rates of new HIV infections and major racial and ethnic disparities in HIV incidence and access to preventive services. In 2021, Dallas County had one of the highest rates of persons newly diagnosed with HIV at 38 per 100,000 population, compared to the national incidence of 11.5 per 100,000 population [18]. The rate of new HIV diagnoses was even higher for Black individuals in the county, at 72 per 100,000 population [19]. Despite the dense HIV epidemic in Dallas County, only 25% of the estimated number of people with indications for PrEP were prescribed it in 2023 [3]. Barriers include high rates of uninsurance and poverty [20,21], medical mistrust and stigma [22,23], low HIV risk perception [15], and high rates of incarceration [24].

About 1 in 7 people with HIV pass through US jails and prisons each year, making the justice system a potentially high-impact setting for HIV testing and prevention [25]. In Texas, the Department of Justice estimated in 2021 that 1.4% of the prison population is living with HIV, which is 4 to 5 times greater than the prevalence in the general US population [26]. Individuals in the criminal legal (CL) system, including those who are in jail, in prison, or under community supervision (ie, probation and parole), also remain at disproportionate risk for HIV infection due to higher rates of sexually transmitted infections (STIs) [27], condomless sex [28,29], transactional sex [30], shared injection drug use equipment [31], dissolution of primary intimate partnerships [32], and broader socioeconomic barriers to medical care (eg, unemployment and homelessness) [33]. Opt-out HIV testing in jails is feasible and can identify many new infections while avoiding the burden of requesting a test among patients [34]. Testing uptake when offered in a nonjudgmental opt-out manner is 80% to 95% [35-37] and should be followed by linking incarcerated individuals to appropriate HIV treatment or preventive care [38-42]. Yet, despite recommendations for the practice of opt-out HIV testing by the Centers for Disease Control and Prevention (CDC), only about a third of US jails offer opt-out HIV testing [43].

Given that most individuals spend less than a month in jail and often cycle multiple times between incarceration and the community [44], there is a high potential public health impact of HIV prevention strategies in jails. Barriers to PrEP implementation in jails exist at several ecological levels and include limited knowledge of PrEP among those likely to benefit and their providers [45,46], lower perceived than actual risk of HIV [47,48], and distrust of institutions [49]. The timing of HIV prevention interventions is also significant, with the transition to living in the community being a particularly pivotal period when HIV transmission–risk behavior is increased and other personal needs take priority during community re-entry [50,51]. For these reasons, effective PrEP implementation strategies in jails may require multiple components to be successful [52-54]. For example, interventions at the individual level have included supporting HIV prevention after incarceration through a mobile app with customized wellness goals and incentives [55]. Building on evidence from CL-involved people with HIV transitioning to the community, peer education and patient navigation are being explored as approaches to improving HIV prevention [56-59]. At the dyadic level, patient-provider shared decision-making around PrEP, which has been used in the community, is also being applied in correctional settings [60-63]. The objective of our study is to assess specific needs and recommended strategies and use these findings to develop, implement, and evaluate a multicomponent PrEP implementation strategy for the Dallas County Jail (DCJ), which is the 8th largest jail in the nation and located in an HIV hotspot [64].

## Methods

### Study Setting

The DCJ is the main jail facility for Dallas County, with 51,000 incarcerated individuals per year (86% men, 48% Black, and 30% Hispanic) and approximately 275 individuals entering and leaving the jail daily. The mean length of stay is 45 days, and 11% of people transfer to prison [65]. Parkland Health, a teaching hospital for UT Southwestern Medical Center, provides health care services at the jail for approximately 6200 patients monthly. Health care for individuals experiencing incarceration is paid for by Dallas County.

Of over 12,000 HIV/STI tests performed each year at the DCJ, there are approximately 50 to 100 new HIV diagnoses (personal communication by [name], April 2024) and high STI positivity (5% syphilis, 5% gonorrhea, and 11% chlamydia) [35,66], which is a recommended indication for PrEP use. The approach to HIV testing at the DCJ is a combination of opt-in and opt-out. All persons entering the jail complete a nursing intake questionnaire to review medical history, receive the option for HIV/STI testing (opt-in), and, for men, indicate if they want to be in separate housing for MSM as a safety precaution. All individuals who undergo blood draws are offered opt-out HIV testing. Individuals with negative HIV test results are not routinely counseled about the results, and few, if any, receive information about PrEP. Currently, new initiation of PrEP is not permitted at the DCJ, and thus, the study will focus on linkage to PrEP after release.

### Study Design

This is a type 3 hybrid implementation-effectiveness study, which takes a combined approach in assessing implementation while also gathering information about clinical outcomes associated with implementation [67]. We will track established implementation outcomes (eg, feasibility, acceptability, and penetration), effectiveness (eg, attending PrEP visits and new HIV/STI diagnoses), and sustainability, including integration into routine processes at collaborating agencies and duration of any positive effects in care processes and outcomes. We will use the EPIS (exploration, preparation, implementation, sustainment) framework [53,54] to guide our efforts to identify and address performance gaps in DCJ PrEP care. Although originally developed for public service sectors, the EPIS framework has since been widely applied in health care, including in jails [54]. As shown across the top portion of Figure 1, our key study concepts and activities reflect EPIS framework components.

**Figure 1 figure1:**
[figure not shown]
Conceptual socioecological model of pre-exposure prophylaxis (PrEP) implementation for criminal legal–involved people. EHR: electronic health record.

### Study Aims

#### Aim 1: Exploration

Using the socioecological model as a conceptual model [68], we will identify and describe specific individual, interpersonal, and community/structural factors that influence PrEP implementation through qualitative interviews and focus groups with key stakeholders in the jail and Dallas community (Figure 1).

##### Participant Characteristics and Recruitment

Participants will be individuals aged 18 years or older who are medical providers or administrators in the DCJ or in the surrounding community, people formerly incarcerated in the DCJ, representatives of community-based organizations serving those affected by HIV or with criminal justice involvement, and members of the public health department. Of note, due to restrictions on recording individuals at the DCJ and due to the benefit of addressing the postincarceration transition, the individuals we recruit will be formerly incarcerated rather than currently incarcerated. Formerly incarcerated individuals will be referred by their health care providers in community clinics or can self-refer in response to Institutional Review Board (IRB)-approved flyers posted in community-based service organizations. Health care professionals will be recruited at routine staff meetings and via email invitations. Administrators will be contacted about participation via email or personal contact from members of the study team.

##### Data Collection

We will conduct 20 to 30 semistructured interviews, which, based on our previous work, should be sufficient to reach saturation (ie, the point at which no new information is being uncovered through additional interviews). Individual interviews are preferred for formerly incarcerated individuals, jail staff, and members of community organizations due to the sensitive nature of questions and the convenience of scheduling.

Separately, we will also conduct a focus group with 10 to 12 members of the HIV/AIDS Re-Entry Coalition (HARC) in Dallas County during one of their quarterly teleconferenced meetings. The HARC is a group comprised of individuals from diverse community organizations who regularly collaborate to enhance the delivery of health and supportive services to individuals who have been recently released from incarceration. Feedback is especially valuable from these group discussions given the breadth and length of experience of the members. Lastly, we will conduct 2 focus groups during a summit event in which we will invite PrEP-providing organizations to compare their experiences and challenges in providing PrEP and related services amid the dynamic funding landscape and to assess opportunities for collaboration.

Semistructured interview and focus group guides will be tailored to each target group, and topics will reflect the range of factors relevant to PrEP implementation across different socioecological levels, as shown in Figure 1. All participants will also be asked to provide feedback on how to adapt and optimize the components of our implementation strategy for local populations, settings, resources, and norms. All interviews and focus groups will be audio recorded and conducted by research staff experienced in qualitative methods.

##### Data Analysis

We will conduct both a rapid qualitative analysis during data collection and a systematic thematic analysis when all data have been collected. The purpose of the rapid analysis is to promote consistent data capture, facilitate communication among the members of the research team about findings, and monitor progress toward saturation [69]. The thematic analysis will systematically categorize patterns in findings across interviews within a group (eg, patients) and across groups (eg, patients, jail providers, and health care leaders), using iterative thematic analysis in accordance with best practice techniques [70,71]. All data will be managed in NVivo 12.0 (QSR International). The study’s principal investigators in conjunction with a study co-investigator who is an established qualitative methodologist will jointly develop a thematic codebook based on a review of the rapid analysis data and 20% of the interview fieldnotes, with codes mapped to the socioecological model presented as part of Figure 1. Trained research staff will double-code all interview transcripts, resolving discrepancies through discussion and conferring with the qualitative co-investigator as needed. A synthesis of the major findings will be presented to stakeholder groups to confirm appropriateness [72].

#### Aim 2: Preparation

In aim 2, our qualitative findings from aim 1 will inform the refinement of a multicomponent PrEP implementation strategy for CL-involved individuals. We will adapt and hone approaches to identify incarcerated people at increased risk for HIV using electronic health record (EHR) clinical decision support tools and patient-reported data to prompt providers to conduct HIV/STI tests and discuss PrEP with those most likely to benefit; engage CL-involved individuals in shared decision-making about PrEP using adaptations of previously developed patient decision aids; and navigate these individuals to existing PrEP services in the Dallas area after release.

##### Datasets to Identify Individuals at Increased Risk for HIV

The Parkland Center for Clinical Innovation (PCCI) has developed and validated an automated matching algorithm to extract data from the DCJ EHR (PEARL) and match it to data from Parkland’s EHR (Epic) from 2010 to the present. Records will be matched based on multiple variables, including patient name, preferred name, date of birth, gender, sex assigned at birth, race or ethnicity, and social security number as available. We will exclude any individuals younger than 18 years. Individuals may have multiple encounters in both the jail and Parkland EHRs due to repeat jail incarcerations or medical visits, and these data will be incorporated as summary variables (eg, number of prior episodes of gonorrhea) with statistical adjustments for repeated measures in an individual. This combined dataset will provide rich data for identifying PrEP candidates and allow us to develop an HIV prediction model. This component of the study will involve the collection of existing data and the development of tools and protocols, and therefore, a waiver of consent will be obtained. Furthermore, matching of records using the identifiers above will be performed behind the firewall of the PCCI, and all datasets will be deidentified prior to sharing with the rest of the research team.

##### Validation of the HIV Risk Prediction Model

We will use our prior models for predicting incident HIV [73,74] to identify candidate variables for our HIV prediction model. Subsequently, the use of temporal validation will assess how well our model will perform prospectively, dividing our dataset into a derivation dataset (2015-2021) and a validation dataset (2022-present). We will train our model to predict incident HIV diagnoses, defined as positive HIV screening and confirmatory tests or new HIV diagnosis codes without prior evidence of HIV in the EHR [73-75]. We will have ample data on new HIV diagnoses to train our models, as Parkland has a robust HIV testing program and diagnoses more new cases of HIV than any other entity in Dallas [76]. Jail EHR data may be more limited in scope because the jail generally provides short-term episodic care. However, given high recidivism rates [77], many incarcerated individuals will have multiple data points in the jail EHR to inform HIV risk prediction, including data on prior HIV/STI testing and substance use.

We will compare the performance of parsimonious versus full models in the validation dataset based on their ability to discriminate between patients with and those without incident HIV using the C-statistic or area under the receiver operator characteristic curve and the Hosmer-Lemeshow goodness of fit test. Additionally, we will use multiple complementary approaches for estimating HIV risk to capture the greatest number of individuals with indications for PrEP. This will include anyone who identifies as transgender, requests MSM housing, has had a recent STI, or opts-in for HIV/STI testing, in addition to those flagged by our EHR model. We will compare EHR models against these criteria to measure the added value of each approach (eg, number of individuals identified by our model as likely to benefit from PrEP who are missed by patient-reported data and vice versa).

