##### Protocol Development

In conjunction with our risk prediction model, the findings from our aim 1 stakeholder interviews will directly inform our protocol for identifying persons who are at increased risk for HIV and likely to benefit from PrEP. This will include elements, such as which practitioners receive EHR alerts about potential PrEP candidates and the content of staff trainings for collecting and acting on patient-reported data and EHR alerts. We will select a final process for identifying candidates for PrEP discussions based on sensitivity (ie, missing as few persons at increased risk as possible), feasibility, and efficiency, while taking into account priorities identified by stakeholders in aim 1.

A key consideration for sexual health discussions in the jail setting is privacy. Feedback in aim 1 will inform how and where these discussions will take place. Providers may also desire additional training in assessing sexual risk, as knowledge of PrEP among correctional nursing staff and clinical providers is vital for successful implementation [78]. Furthermore, the approach to incarcerated individuals about sensitive topics, such as sexual health and substance use, will be informed by best practices, including having these screenings conducted one-on-one by medical staff and partnering with community-based organizations [79]. Any paper materials given to patients will be adapted to the American Medical Association’s recommended 6th grade reading level and worded to avoid disclosing the health status.

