**Figure 2 figure2:**
[figure not shown]
Intervention steps in the jail-to-community continuum. DCJ: Dallas County Jail; EHR: electronic health record; PrEP: pre-exposure prophylaxis; STI: sexually transmitted infection.

In the “identify” step, when individuals enter the jail, a jail EHR record will be created (or an existing record will be opened for those with prior DCJ incarceration). Our automated algorithm will match the jail EHR to the Parkland EHR and generate an individual HIV risk score. For people with predicted HIV risk above a prespecified threshold that maximizes sensitivity without causing alert fatigue among providers, an automated prompt will appear in the jail EHR for providers to discuss PrEP and order HIV/STI testing. As illustrated in Figure 2, providers will also be prompted to order HIV/STI tests for any patients who report risk factors at intake or during a clinical assessment (eg, transgender identity and requests to be housed with MSM) or who request testing directly. Prompts will persist until orders are completed as a “nudge,” a behavioral economic intervention to maximize ordering [83], and results are entered into the EHR.

In the “engage” step, positive HIV tests will prompt referrals to the jail HIV clinic for rapid initiation of antiretroviral therapy according to the current practice, and STIs will be treated based on CDC guidelines [84]. Persons with negative HIV tests will meet one-on-one with a provider or PrEP navigator and receive counseling informed by our PrEP decision-support tool. The navigator we hire will be experienced in working with CL-involved people. Counseling will be person-centered and culturally tailored, with positive sexual health framing.

In the “navigate” step, for patients interested in PrEP, the navigator will review a list of PrEP clinic locations and assist with selecting a provider. Once an individual is released from the DCJ, the navigator will facilitate PrEP linkage by contacting that individual (by phone or SMS text messaging) and providing personalized care navigation. A hotline will be available for released individuals to call for assistance with PrEP referrals. The navigator will continue to follow referred patients for 3 months after any PrEP initiations, recording these contacts and clinical outcomes in REDCap, a secure online data capture system [85].

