## Results

The study was funded by the National Institute of Mental Health in April 2022. Progress has been made on various aims to date. Qualitative interviews have been completed with 26 individuals, including 9 formerly incarcerated individuals, 9 county jail staff, and 9 employees of community organizations (1 individual was both a formerly incarcerated individual and an employee of a community organization). A focus group with 10 additional individuals has also been conducted. All interviews have been transcribed, coded, and analyzed, and a manuscript highlighting the key themes is in progress.

In addition, summaries of field notes for each interview have been organized into key barriers; facilitators; suggested approaches to overcome barriers; resources needed to overcome barriers; and specific strategies to improve risk assessment, HIV testing, sexual health or PrEP education during incarceration, and postrelease linkage to PrEP. Findings from these interviews have been applied to formulate a jail PrEP implementation protocol using rapid qualitative analysis.

An HIV risk prediction model based on jail EHR data to identify individuals most likely to benefit from PrEP has been developed using records from 33,458 individuals who have undergone HIV testing in jail. This model has been optimized using machine learning, has been internally validated, and is ready to be deployed. Future exercises will include integration with health system EHR data from Parkland Hospital and comparisons to parsimonious models, which will guide the iterative development of the model. We anticipate that preliminary study findings on the implementation and effectiveness of the jail PrEP implementation strategy will be available in 2026. 

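### The Hosmer-Lemeshow test is listed, beside the C-statistic, as a way to compare the risk models on discrimination; it tests calibration, cannot rank two models, and should be replaced

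*Protocol article*

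**What the plan says.** Under Validation of the HIV Risk Prediction Model, the parsimonious and full models are to be compared in the temporal validation set (2022 onward) "based on their ability to discriminate between patients with and those without incident HIV", and the tools named are "using the C-statistic or area under the receiver operator characteristic curve and the Hosmer-Lemeshow goodness of fit test". No other calibration measure is named, and nothing says how the two statistics are weighed if they disagree.

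Three other places bear on how the result is used:

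- Steps for Strategy Implementation: a prompt appears for people with predicted risk "above a prespecified threshold that maximizes sensitivity without causing alert fatigue among providers".
- Protocol Development: "We will select a final process for identifying candidates for PrEP discussions based on sensitivity", together with feasibility, efficiency and stakeholder priorities.
- Results: a model has been "developed using records from 33,458 individuals who have undergone HIV testing in jail". Linking in the Parkland records and comparing with parsimonious models are still to come, and that comparison will guide further development.

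Potential Limitations and Alternative Approaches adds that, if the model performs poorly, identification will rest mainly on patient-reported data.

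**The concern.** Discrimination is whether people who acquire HIV get higher scores than those who do not. Calibration is whether the predicted risks match the observed frequencies. The sentence assigns a calibration test to the discrimination question. This is a named method attached to the wrong property, not a detail left for a fuller document.

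Three features make the test a poor choice even for calibration here. It returns a p-value, with no size or direction of error. Two p-values from two models do not rank them. And with a rare outcome its power changes greatly with the number of records, which will itself change when Parkland data are linked in.

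At stake are two decisions still ahead: which model is carried forward, and whether performance is good enough to rely on the model at all. For the second, a p-value could be read as an absolute pass or fail.

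**Working it through.** The article states no validation size, C-statistic or Hosmer-Lemeshow result, so there is no figure to reproduce. The check is whether the test behaves as the sentence needs.

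**Inputs from the article**

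- Event rate, from Study Setting: "Of over 12,000 HIV/STI tests performed each year at the DCJ, there are approximately 50 to 100 new HIV diagnoses". This gives 50/12,000 = 0.42% to 100/12,000 = 0.83%. The denominator mixes HIV and STI tests, so this is approximate. The power paragraph under Sustainment implies 3/250 = 1.2%.
- 33,458 individuals used to develop the jail-data model (Results).

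**Assumptions**

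- Validation size n from 3,000 to 100,000.
- True model logit(p) = a + 1.1x with x standard normal, which gives AUC of about 0.78.
- Miscalibration of the sizes shown below.
- Hosmer-Lemeshow statistic = sum over 10 risk groups of (O − E)² / [E(1 − E/n_g)], where O and E are observed and expected events and n_g the group size. It is referred to chi-square with 10 df (external validation) at 0.05.
- 300 runs per cell, so the Monte Carlo standard error is at most √(0.25/300) = 2.9 percentage points.

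**Step 1: does the test track discrimination?** At n = 24,000 and a rate of 75/12,000 = 0.625% (about 150 events):

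| Model | AUC | Rejected |
|---|---|---|
| Uninformative, calibrated | 0.50 | 5% |
| Informative, over-predicts two-fold | 0.78 | 100% |

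Ranking on this test would prefer the model that cannot tell cases from non-cases.

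**Step 2: how much does the verdict move with n for a fixed misfit?**

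| Rate | Misfit | 3,000 | 12,000 | 24,000 | 33,458 | 100,000 |
|---|---|---|---|---|---|---|
| 0.42% | O/E about 0.8 | 3% | 4% | 18% | 25% | 87% |
| 0.83% | O/E about 0.8 | 4% | 14% | 41% | 71% | 100% |
| 0.42% | slope 0.8 | 17% | 38% | 83% | 93% | 100% |
| 0.83% | slope 0.8 | 18% | 77% | 99% | 100% | 100% |

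The AUC stays at about 0.78 throughout. The slope rows keep a fixed while the predicted coefficient becomes 1.1/0.8 = 1.375, so they also over-predict on average: O/E is roughly exp[(1.1² − 1.375²)/2] = exp(−0.34) = 0.71. They are therefore a larger misfit than slope alone. Rerunning the two O/E 0.8 rows with another random seed changed no cell by more than 7 points.

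**Step 3: is n the only driver?** No. A calibrated model was rejected in 3% to 8% of runs at n of 12,000 or more, and in 9% to 11% at 3,000, where events are sparse (3,000 × 0.42% = about 12.5). At n = 12,000 and a rate of 0.42%, rejection ran from 4% at O/E 0.8 to 97% at O/E 0.5.

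**Step 4: does such misfit change who is flagged?** Each simulated distortion is a monotone shift of the score. It leaves the ranking intact, so at a fixed number of alerts the same people are prompted. If the cut-off were instead a fixed absolute risk, the shift would change alert volume and sensitivity. Hosmer-Lemeshow would report neither the direction nor the size of the error behind that change.

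**The case against.** The strongest reply is that the sentence is only loosely worded. It opens by promising a comparison of performance and names the C-statistic first. Pairing it with Hosmer-Lemeshow for fit is a familiar, if dated, convention. Both models would be scored on the same validation set, so n does not differ between them. No cut-off or pass/fail rule for the test is stated, and the comparison feeds iterative development rather than a single selection. The remedy's finer detail could sit in a fuller document.

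Most of this stands, and it limits the harm that can be claimed. It does not rescue the test: a shared n does not make two p-values a ranking, and a shared n does not help when the question is whether one model is good enough in absolute terms.

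A reader might infer three stronger things that the documents do not support:

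- **That the test sets the alert threshold.** The threshold is tied to sensitivity and alert fatigue, and the identification process to sensitivity, feasibility and efficiency.
- **That the verdict is fixed by sample size alone.** Step 3 shows it depends on the misfit too.
- **That the wrong model will be chosen.** Nothing lets Hosmer-Lemeshow override the C-statistic, and nothing ties the fallback to patient-reported data to this test. Patient-reported routes also run alongside the model.

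**Conclusion.** The point holds in limited form. A calibration test is listed as a means of comparing discrimination. It cannot do that job, and it is a weak summary of calibration for a rare outcome: the same O/E of about 0.8 would pass in 97% of runs at 3,000 records and fail in 87% at 100,000, at the 0.42% rate. A mistaken model choice, or a mistaken judgement that performance is inadequate, is possible because the weighing of the two statistics is left open; neither is shown. The rejection rates rest on assumed validation sizes, AUC and misfit. The qualitative finding in Step 1 follows from what the test measures. This is a modest correction, worth making because the comparison has not yet been run.

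**What to change.** Rewrite the sentence so that each property has its own measure, all in the 2022-onward validation set:

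1. **Discrimination:** C-statistic with a confidence interval.
2. **Calibration:** replace Hosmer-Lemeshow with calibration intercept and slope, each with a confidence interval, and a smoothed calibration plot.
3. **Choice between the parsimonious and full models:** sensitivity and positive predictive value at the same alert volume for both, with a paired bootstrap confidence interval for each difference. This carries the sensitivity and alert-burden criteria already in Protocol Development and Steps for Strategy Implementation into the model comparison.

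The cost is a change of wording and a small amount of extra analysis on data already held. No new data collection is needed.
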